### Data analysis

#### Descriptive statistics

A study on prevalence of “job burnout” in the population will be performed, as well as on their socio-demographic characteristics and work conditions.

Quantitative variables will be described according to their measures of central tendency, mean, and confidence intervals in the case of normal distributions, and by their median and interquartile range in the case of non-normal distributions.

Percentages and confidence intervals will be obtained for qualitative variables.

#### Analytical statistics

Initial comparability between the intervention and control groups will be analyzed with the Student's t-test in the case of independent data of quantitative variables (age, years of experience, workload, scores from the questionnaires, etc.) that fit a normal distribution, with the Mann-Whitney U non-parametric test for those not fitting a normal distribution, and with contingency tables in the case of qualitative variables (sex, marital status, professional group, type of contract, etc.).

Univariate correlations between socio-demographic and work characteristics of subjects and their score in the MBI at the beginning of the trial, as well as the correlation between the mentioned characteristics and the change observed during the follow-up, will be analyzed by use of simple linear regression models.

The correlation between the changes associated with burnout syndrome and changes in work-life quality and anxiety, as perceived by health professionals, will be measured using the correlation coefficients for score changes from the MBI, the professional quality of life questionnaire (QPL-35), and Goldberg's GHQ. Pearson's r will be used in the case of normal distributions, and Spearman's rho for non-normal distributions.

Explanatory models will be built to identify work and occupational characteristics related to work satisfaction and burnout. The dependent variable will be the score obtained from the relevant questionnaires at baseline, and the independent variables those considered as relevant in previous theoretical models or proven significant in the univariate analysis.

A comparison of average scores on the MBI will be performed between the intervention and control groups after the intervention and at the end of the follow-up in order to measure the effectiveness of the intervention, and the Student's t-test will be employed for independent data. Confidence intervals of 95% will be calculated for the differences. If the application criteria are not met for that analysis, non-parametric tests will be used (Mann-Whitney U test).

An explanatory model will be constructed to provide an answer to the principal objective, the dependent variable will be score on the MBI, the main independent variable will be the intervention, and modifying variables will be all those found to be related to burnout in the univariate analysis or the signficant ones in theoretical models. This analysis will complement the first one since it will allow for correcting for confounding factors and analyzing effect modifications.

Since subjects belong to various clusters (health centers), generalized estimating equations (GEE) models will be used to build explanatory models that serve for identifying work and occupational characteristics related to work satisfaction and burnout, or to provide an answer to the principal objective. GEE models correct for non-independence of observations among the same group (health center), assuming *a priori* a certain structure of correlation for the dependent variable measured in each group. In addition, these models are not very stringent about the distribution of the outcome variable and offer standard error measurements of the “robust” coefficients, which are stable even if the correlation chosen *a priori* is incorrect or if the strength of the correlation between the observation changes along the different clusters [22]. In their interpretation, however, they do not allow measuring the influence that a characteristic has on each subject, but they allow for estimating the average of the population response when the independent variables change for the whole population [23].

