### Sample size and sampling

The main outcome variable will be the score on the emotional exhaustion sub-scale of the MBI.

In a previous study performed by this group in the same setting, the average score on this sub-scale was 24, with a standard deviation of 12 points. A change of at least 5 points with respect to the baseline (~20% of the initial value) will be considered significant. These figures do not differ from those found in other populations.

The sample is calculated as non-finite size data, using the formula proposed by Snedecor and Cochran [18].

It is therefore necessary to include ~90 subjects per group, considering a type I error <0.05 and a type II error of 20% (statistical power 80%).

However, we are going to study clusters (health centers) where the variability of the studied parameter will be lower among subjects from the same group and higher among subjects from different groups. This effect, termed the “design effect”, multiplies the needed sample size by a factor ranging from 1.5 to 5. The magnitude of this factor depends on the relationship between the intragroup and intergroup variance, termed the intraclass correlation coefficient [19]. In this case, since there are environmental factors that favor the appearance of burnout, at least moderate intraclass clustering is expected, for which we estimate the design factor will be ~2. Thus, we will need at least 180 subjects per group. If we have a loss to follow-up of ~10%, the studied population will have to be ~200 subjects per group.

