#### Dependent variable

Possible burnout condition as identified by score modification, or change, before and after the intervention on the EE scale of the MBI for each subject and for the whole sample.

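### The analyses of change during follow-up carry no intervention term, so a working intervention can pass for an association with characteristics that differ between the two sets of seven centres

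*Protocol article*

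**What the plan says.** All of this stands in the Protocol article.

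- **Change regressions (Analytical statistics).** For socio-demographic and work characteristics, "the correlation between the mentioned characteristics and the change observed during the follow-up, will be analyzed by use of simple linear regression models". The same sentence applies the method to baseline MBI scores.
- **Change correlations (Analytical statistics).** The link between changes in burnout, quality of working life and anxiety "will be measured using the correlation coefficients for score changes from the MBI", the QPL-35 and the GHQ, by Pearson or Spearman. No arm term or split by arm is given here or for the regressions.
- **Effectiveness model (Analytical statistics).** The model for the principal objective does include the treatment arm, as its main predictor. Its further covariates follow a selection rule: "modifying variables will be all those found to be related to burnout in the univariate analysis or the signficant ones in theoretical models". GEE is named for the explanatory models. It is not named for the simple regressions or the correlations.
- **Outcome (Dependent variable).** The outcome is "score modification, or change, before and after the intervention on the EE scale of the MBI for each subject and for the whole sample".
- **Size of effect (Sample size and sampling).** In an earlier study "the average score on this sub-scale was 24, with a standard deviation of 12 points". For this trial, "A change of at least 5 points with respect to the baseline (~20% of the initial value) will be considered significant".

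**The concern.** The trial is designed to cause change in one arm only. A one-predictor model of change over both arms leaves that cause out. If a characteristic differs between the arms, part of the intervention effect is credited to it. The correlations have the same weakness: if the training moves both scores, the pooled coefficient partly reflects trained against untrained staff.

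Only 14 centres are randomized. They are paired on number of professionals, socio-economic area and urban or rural setting. Shift work, workload and contract type are not pairing factors and may well vary by centre, so a sizeable chance imbalance is plausible.

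What is at stake is the answer to which characteristics, and which other scores, go with change. That answer is least reliable when the training works. There may also be a knock-on effect on covariate selection for the effectiveness model.

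**Working it through.** **Inputs from the protocol:** EE mean 24, SD 12; effect 5 points; design effect about 2; 14 centres, 7 per arm; about 180 analysed per group.

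**Assumptions (not in the protocol):** SD of change 8.5 to 15, with 10.7 = 12 × √(2 × (1 − 0.6)) for a pre-post correlation of 0.6; share of a characteristic's variance lying between centres (trait ICC) 0 to 1. Within-pair similarity of traits was not modelled.

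**1. The plan's own figures.** n = 2 × (1.96 + 0.84)² × 12² / 5² ≈ 91 per group; doubled, 182; 180 / 0.9 = 200. The stated ~90, 180 and ~200 are reproduced. With 360 / 14 = 25.7 per centre, a design effect of 2 implies an outcome ICC of 1 / (25.7 − 1) = 0.04.

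**2. A simple case.** A trait with no effect of its own is present in 5 of 7 intervention and 2 of 7 control centres of equal size. The pooled regression shows 5 × (5/7 − 2/7) = 2.1 points.

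**3. Closed form.** A null trait differs by d within-arm SDs between arms.

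- Slope per SD = 5 × (d/4) / (1 + d²/4).
- r = (d × δ/4) / √((1 + d²/4)(1 + δ²/4)), with δ = 5 / SD of change.
- False-hit rate = 1 − Φ(1.96 − z) + Φ(−1.96 − z), with z = r√358 / √(1 − r²).

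At SD of change 12:

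| d | Slope (points per SD) | False-hit rate |
|---|---|---|
| 0.2 | 0.25 | 6.7% |
| 0.3 | 0.37 | 8.9% |
| 0.5 | 0.59 | 15.6% |
| 1.0 | 1.00 | 41% |

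At d = 0.5 the rate runs from 11.8% (SD 15) to 25.6% (SD 8.5).

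**4. Simulation over randomizations.** 14 centres of 26, effect 5, null trait, ordinary regression of change.

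| Outcome ICC | SD of change | Trait ICC | No arm term | With arm term |
|---|---|---|---|---|
| 0 | 10.7 | 0.3 / 0.5 / 1 | 9% / 12% / 22% | about 5% |
| 0 | 12 | 0 | 4.7% | 5.0% |
| 0 | 12 | 0.2 | 7.7% | 5.0% |
| 0 | 12 | 1 | 17.8% | 5.4% |
| 0.04 | 12 | 0 | 4.6% | 4.8% |
| 0.04 | 12 | 0.2 | 9.6% | 6.9% |
| 0.04 | 12 | 1 | 27.3% | 17.3% |

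In the last row the arm term removes 27.3 − 17.3 = 10 percentage points. The remaining 17.3% comes from ignoring clustering: with no intervention effect at all, the same setting gives 17.2% without the arm. In the most unbalanced fifth of trials, mean d is about 0.19 for an individual-level trait and about 0.94 for a centre-level one.

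**5. Correlations of changes.** If the within-arm correlation is 0, pooled r = 0.25 × d1 × d2 / √((1 + 0.25 d1²)(1 + 0.25 d2²)). With d1 = 5/12 = 0.42 and an assumed effect d2 = 0.42 to 0.8 on the second score, r = 0.042 to 0.076. If the within-arm correlation is 0.30, the pooled value is 0.33 to 0.35.

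**6. Carrying false hits into the effectiveness model.** With the intervention in the model and the trait added whenever it was significant in the pooled change regression, mean estimates at outcome ICC 0.04 ran from −4.85 to −5.04 against a true −5, with SD about 1.8 throughout. The largest shift was for a centre-level trait, from −4.96 to −4.85, or 0.11 points.

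**The case against.** **Pooling is inferred.** The text never says that both arms are analysed together, and a condensed article may leave a split by arm to the full plan. This stands as a caution. Still, the same section names the two groups where it compares them and does not name them here, and the method it does name has room for one predictor only.

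**Clustering methods already absorb much of this.** Arm is assigned by centre, so an omitted arm effect behaves like between-centre variance. At outcome ICC 0, SD 10.7 and trait ICC 0.3 / 0.5 / 1, without any arm term, a random-centre model gave 4.2% / 5.4% / 2.1%, regression on centre means 4.7% / 4.8% / 4.0%, and uncorrected cluster-robust errors 6.2% / 7.4% / 10.2%. This largely stands for the error rate, and it rules out the stronger claim that correcting for clustering leaves the problem untouched. It does not undo the shift in the estimate in a trial with a realised imbalance, and the plan does not assign GEE to these analyses.

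**Most listed control variables are personal.** Age, sex, marital status and similar traits vary mainly between individuals, where the rate stays near 5%. Pairing may also reduce centre-level imbalance. Both points stand.

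**Effect on the main result.** A reader might infer that false hits necessarily enter the effectiveness model and distort the treatment effect. The protocol does not support this. Its rule, "modifying variables will be all those found to be related to burnout in the univariate analysis", does not say which univariate analysis is meant. It may be the baseline-score regressions, in which no intervention effect can exist. In either case the model contains the intervention.

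**Conclusion.** The point holds for the predictors-of-change regressions and the correlations of changes, if these are pooled as the wording suggests. It is material for characteristics that vary strongly by centre: false-hit rates of about 9% to 22% at trait ICC 0.3 to 1, against about 5% with the arm included. At moderate individual-level imbalances it is slight. For correlations the rise is small and depends on the training also moving the second score. Part of the excess error is ignored clustering, so the arm term and centre-level variance are both needed.

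The SD of change, the trait ICCs and the effect on the second score are assumptions. The documents do not support reading this as a threat to the effectiveness estimate, or as a fault affecting every characteristic alike. It is an inexpensive improvement to supporting analyses.

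**What to change.** 1. Model change as characteristic plus arm, with the centre-level GEE variance the plan already uses for its explanatory models. With 14 centres, uncorrected robust errors run somewhat high for centre-level traits, so a small-sample correction is sensible.
2. Report correlations of score changes separately by arm, or as partial correlations given arm.
3. State that covariates for the effectiveness model come from the baseline-score regressions or from theory, not from the unadjusted change regressions.

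Regressions on baseline scores need no arm term. The cost is one degree of freedom per model and a change of wording. Sample size, data collection and trial conduct are unaffected.

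### The univariate regressions ignore clustering by health centre, so p-values are too favourable for characteristics that differ between centres

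*Protocol article*

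**What the plan says.** All of this is in the protocol article.

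- **Sample size and sampling.** Scores are expected to be correlated within health centres: "at least moderate intraclass clustering is expected, for which we estimate the design factor will be ~2".
- **Analytical statistics, univariate step.** Associations of professionals' characteristics with baseline MBI score, and with how that score changes over follow-up, "will be analyzed by use of simple linear regression models". No term or variance correction for centre is mentioned.
- **Analytical statistics, use of the results.** The baseline explanatory models take as independent variables "those considered as relevant in previous theoretical models or proven significant in the univariate analysis". In the model for the principal objective, "modifying variables will be all those found to be related to burnout in the univariate analysis or the signficant ones in theoretical models".
- **Analytical statistics, clustering.** Because professionals belong to centres, "generalized estimating equations (GEE) models will be used to build explanatory models", with robust standard errors. This covers both the models of burnout correlates and the model for the principal objective. The univariate step is not included.

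**The concern.** The plan recognises within-centre correlation when it sizes the trial and when it builds the explanatory models, but it fixes a method that assumes independence for the step between them. If a characteristic differs between centres, simple regression credits it with more independent information than the data hold. Its standard error is then too small and its p-value too low.

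Two things are at stake. The univariate associations may be reported with intervals that are too narrow. A characteristic may also enter an explanatory model because of a chance difference between centres. Refitting by GEE gives the selected variables a better standard error but does not undo the selection.

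**Working it through.** **Reproducing the plan's figures.** With a difference of 5, SD 12, two-sided 5% and 80% power (sidedness is not stated, but two-sided matches), n = 2 × (1.96 + 0.84)² × 12² / 5² ≈ 90.4, which rounds up to 91 per group against the stated ~90. Then 90 × 2 = 180, and 180 / 0.90 = 200. The stated figures hold.

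**Outcome ICC implied by the design factor.** With 14 centres and 360 professionals after losses, m = 360 / 14 = 25.7. From design factor = 1 + (m − 1) × ICC, ICC = (2 − 1) / 24.7 ≈ 0.04. With all 400 at baseline, m = 28.6 and ICC = 1 / 27.6 ≈ 0.036. The product (m − 1) × ICC is 1 either way, so the choice of m hardly matters below. Equal centre sizes are assumed.

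**Effect on a simple-regression slope.** Variance inflation (VIF) is about 1 + (m − 1) × ICC of outcome × ICC of covariate. The real level of a nominal 5% test is 2 × P(Z > 1.96 / √VIF). The documents give no covariate ICCs, so the first column is an assumed range. Outcome ICC is 0.04 and m is 25.7.

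| Covariate ICC (assumed) | VIF | Standard error too small by (1 − 1/√VIF) | Real level |
|---|---|---|---|
| 0.05 | 1 + 24.7 × 0.04 × 0.05 = 1.05 | 2% | 5.6% |
| 0.3 | 1 + 24.7 × 0.04 × 0.3 = 1.30 | 12% | 8.5% |
| 0.5 | 1 + 24.7 × 0.04 × 0.5 = 1.49 | 18% | 10.9% |
| 1 (constant within centre) | 1 + 24.7 × 0.04 × 1 = 1.99 | 29% | 16.5% |

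A simulation with 14 centres of 29 professionals and 20,000 runs per setting gave 5.6%, 8.6%, 10.5% and 17.0% for the same four rows. It gave 5.0% for a covariate unrelated to centre.

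**Which row applies.** Every item under Control variables is recorded on the individual professional. Workload and shift working could plausibly depend on the centre, but the article does not say that they do. The truly centre-level features (number of professionals, socio-economic area, urban or rural setting) are used to pair centres in the Randomization section and are not in the Control variables list.

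**The case against.** The strongest reply is that this is a screening step whose errors are largely caught later, and most of that reply stands.

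- Selected variables are re-estimated by GEE with clustering allowed for, and theory is a separate entry route that does not depend on these p-values.
- The GEE model for the principal objective is described as complementing the direct between-group comparison, which uses no screened covariates.
- No significance threshold is given for entry into that model, so 5% is only a benchmark there. Univariate significance is named as a criterion for the baseline models.
- The design factor was set for the emotional exhaustion score. Applying its ICC to change scores is an assumption.

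A reader might infer that the flawed screen distorts the estimated intervention effect. The documents do not support that: an unneeded covariate in a randomised comparison mainly affects precision and model choice, and does not bias the effect in expectation. A reader might also infer that the full design factor, and so the 16.5%, applies to workload or shift working. That would need those variables to be constant within a centre, which the article nowhere states.

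Two things remain. The univariate results themselves stay uncorrected, and selection still rests partly on p-values from a method that contradicts the plan's own clustering assumption. The method is stated outright, so it is not a detail left to a fuller document.

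**Conclusion.** The inconsistency is real and minor. For characteristics little related to centre the error is negligible (about 5.6% at a covariate ICC of 0.05). For partly centre-driven ones it is moderate (about 8.5% to 10.9% at 0.3 to 0.5). The 16.5% figure is an upper bound that no listed variable is shown to reach.

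These sizes rest on an outcome ICC of about 0.04, taken from the stated design factor and assumed to hold for change as well, and on covariate ICCs that are assumptions throughout. Ignoring the correlation affects standard errors and p-values; it does not by itself bias the slopes. Clustering matters more for the Student's t-test of effectiveness in the same section, because there the exposure is fixed at centre level.

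**What to change.** In Analytical statistics, replace simple linear regression in the univariate step with single-characteristic GEE (or mixed) models grouped by health centre, for both baseline score and change. State a small-sample correction for 14 centres, both here and for the explanatory models. The latter currently name only robust standard errors, and with so few clusters uncorrected robust errors can themselves be too small. Prespecifying the covariates would also remove the selection part of the problem, though not the error in the reported univariate results.

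The change is to wording only and needs no new data, since GEE is already planned. The downside is somewhat wider intervals for centre-driven characteristics.

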## Methods/design

### Design

Controlled, pragmatic, randomized clinical trial with an intervention and control group that will not present differences in any studied characteristics *a priori*.

All medium to large size HCCs from the area will be offered participation and randomly allocated, 7 to the intervention group and other 7 to the control group.

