### Randomization

The HCCs that accept to participate will be grouped in pairs based on 3 features: number of professionals, socio-economic area, and urban or rural environment. One center from each pair will be randomly allocated into intervention or control group, and the paired center into the opposite group (allocation by blocks of size 2).

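### Effectiveness is tested as if the health professionals were independent although 14 matched centres are randomised; a centre-clustered GEE is planned too, but nothing says it decides

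*Protocol article*

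**What the plan says.** All references are to the protocol article.

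- **Unit of randomisation.** Under Design, centres are "randomly allocated, 7 to the intervention group and other 7 to the control group". Under Randomization they are first matched on number of professionals, socio-economic area and urban or rural setting; then "One center from each pair will be randomly allocated into intervention or control group", and its partner goes to the other arm.
- **Clustering in the sample size.** Sample size and sampling expects at least moderate clustering by centre, "for which we estimate the design factor will be ~2", and moves from about 90 to 180 people per group, then to about 200 for 10% loss.
- **Effectiveness test.** Analytical statistics compares average MBI scores between arms after the intervention and at the end of follow-up as its measure of effectiveness, and for this the Student's "t-test will be employed for independent data". It adds: "Confidence intervals of 95% will be calculated for the differences". If the conditions for the t-test fail, "non-parametric tests will be used (Mann-Whitney U test").
- **Model.** The section then describes an explanatory model for the principal objective, with the intervention as main independent variable: "This analysis will complement the first one since it will allow for correcting for confounding factors". The next paragraph says that, because people belong to centres, GEE models will be used for the explanatory models or for the principal objective, with robust standard errors.

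**The concern.** The sample size treats colleagues in one centre as correlated; the test attached to effectiveness treats them as independent. Both cannot hold. With positive correlation inside centres, the t-test's standard error is too small, its interval too narrow and its p-value too low. Mann-Whitney U has the same fault.

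The GEE is the right kind of analysis for this design, but the text makes it a companion to the t-test, and the reason first given is confounding and effect modification. Two results for the same question can therefore be reported, and nothing says which one stands if they disagree. When the workshop has no effect, the unadjusted test is the one more likely to give a significant result. At stake is whether a claim of effectiveness carries the 5% error rate on which the trial was sized.

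**Working it through.** **Inputs from the article:** SD 12, difference 5 points, type I error 0.05, power 80%, design effect (DE) about 2, 10% loss, 7 centres per arm. Sidedness is not stated; two-sided is assumed because it reproduces the stated size (one-sided gives 72 per group).

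**1. Reproduce the plan's sample size.**
n = 2 × (1.96 + 0.84)² × 12² / 5² ≈ 90.4, so 91 per group (stated: about 90). Times 2 = 182 (stated: at least 180). 180 / 0.90 = 200 (stated: about 200). The plan therefore uses the design effect as a variance inflation of 2 on the comparison of arms.

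**2. Type I error of a test that ignores centre.**
The true standard error is √DE times the one the test uses, so
type I = 2 × [1 − Φ(1.96 / √DE)].
At DE = 2: 1.96 / 1.414 = 1.386, giving 16.6%. Coverage of the nominal 95% interval is 100% − 16.6% = 83.4%.

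**3. Check by simulation.**
180 / 7 ≈ 26 people per centre, so DE = 2 implies an intraclass correlation of 1 / (26 − 1) = 0.04. With 29 per centre (200 / 7) it is about 0.036. With 7 + 7 centres and no true effect, the t-test rejected in 16.2% to 17.0% of runs and Mann-Whitney U in 16.7%.

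**4. Allow for the pairing.**
If the pairs explain a share f of the between-centre variance, the inflation on the arm difference becomes (1 − 0.04) + 26 × 0.04 × (1 − f) = 0.96 + 1.04 × (1 − f). The article gives no value for f, so the range below is an assumption.

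| f | Inflation | 1.96 / √inflation | Type I error |
|---|---|---|---|
| 0 | 2.00 | 1.386 | 16.6% |
| 0.25 | 1.74 | 1.486 | 13.7% |
| 0.50 | 1.48 | 1.611 | 10.7% |
| 0.75 | 1.22 | 1.774 | 7.6% |

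Simulations agree to within about one percentage point: 13% to 14%, 10% to 11% and 7% to 8% for the last three rows.

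**5. Candidate replacements, simulated at DE = 2 with no true effect.**

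| Analysis | No gain from pairing | Pairs explain 25% / 50% / 75% |
|---|---|---|
| t-test on centre means, unpaired, 12 df | 5.0% to 5.3% | 3.8% / 2.7% / 1.8% |
| t-test on centre means, paired, 6 df | 5.0% to 5.4% | about 5% throughout |
| Uncorrected robust variance with a z-test, pairs ignored | about 10% | 7.6% / 5.7% / 4.0% |

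The unpaired centre-level test becomes conservative if the matching works. The uncorrected robust z-test is too liberal with 14 centres if the matching does not help. The paired test holds its level in both cases.

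**The case against.** The strongest reply is that the article does plan for clustering. The GEE paragraph names health centres as the clusters, explains the correction for non-independence and applies it to the principal objective; the t-test is never called primary. On this reading the t-test is the crude step of a crude-then-adjusted sequence, first in order but not in authority, and the formal ranking may sit in a fuller plan that is not shown.

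Much of this stands. A reader who saw only the t-test sentence might infer that the trial ignores clustering in its analysis. That is wrong. A reader might also take 17% as the trial's false-positive rate. It is that only if the t-test decides and the pairing removes no between-centre variance; if the GEE decides, the t-test's error rate is not the trial's. Nor should the error be carried up to a design effect of 5: the article gives 1.5 to 5 as a general range and about 2 as its estimate for this trial.

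The reply does not remove the defect. The article states a test, ties it to effectiveness and gives it an interval and a fallback. This is a stated choice that conflicts with the design, not detail left to another document. The interval is too narrow under any positive clustering that the pairing does not absorb, whatever the t-test's rank. And describing the GEE as a complement leaves the t-test's p-value and interval in place as evidence of effect.

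**Conclusion.** The point holds, with limits. The article attaches effectiveness to an individual-level test for independent data, which contradicts its own randomisation by centre and its design effect of about 2. It also plans a suitable type of analysis, a GEE clustered by centre, but gives it no precedence.

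For the unadjusted test, the size is about 17% type I error and 83% coverage at a design effect of 2 with no gain from pairing, and about 14% to 8% if pairs absorb 25% to 75% of the between-centre variance. These figures assume two-sided testing and similar centre sizes, and the pairing shares are not from the article. The error stays above 5% throughout. It should be corrected before analysis, because the main claim may rest on this comparison and the change is to wording only.

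**What to change.** 1. State that one cluster-aware analysis of the MBI emotional exhaustion score decides effectiveness, and name it in advance. Either will do:
   - the planned GEE with centre as the cluster, a small-sample correction for 14 centres, and the matching pair or the three matching factors in the model; or
   - a paired comparison of centre means (7 pairs, 6 df).
2. Take the reported difference, 95% interval and p-value from that analysis.
3. Remove the t-test and Mann-Whitney U as effectiveness tests. Raw arm means may stay as description, without a test.
4. Reword the sentence that makes the model a complement to the first comparison.

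**Cost.** No new data and no change of design. The interval widens and the p-value becomes less favourable. With SD 12, 180 per arm and a design effect of 2, the unadjusted half-width is 1.96 × 12 × √(2/180) ≈ 2.5 points. With the correct standard error (12 × √(2/180) × √2 ≈ 1.79) and 6 df it is 2.447 × 1.79 ≈ 4.4 points if pairing gains nothing, and less if the matching works.

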### Studied subjects

The studied population is comprised of all health professionals from 14 primary health care teams of in Area 11 of Madrid who accept to participate (a total of 400 subjects are anticipated to be included).

Inclusion criteria: All health professionals (family physicians, pediatricians, and nurses) who are part of the health care centers (HCC) at the moment of the trial.

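### With 7 centres per arm, GEE robust standard errors need a small-sample correction: without one, the nominal 5% error is about 9.5% (roughly 6% to 12%, depending on choices the article leaves open)

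*Protocol article*

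**What the plan says.** - **Clusters.** Under Design, centres are "randomly allocated, 7 to the intervention group and other 7 to the control group". Under Studied subjects, "a total of 400 subjects are anticipated to be included", or about 29 per centre.
- **Pairing.** Under Randomization, centres are matched in pairs on size, socio-economic area and urban or rural setting, and one of each pair is drawn for each arm. The GEE text does not mention the pairs.
- **Error rate.** Under Sample size and sampling, the trial is sized "considering a type I error <0.05 and a type II error of 20% (statistical power 80"%), with a design effect of about 2 because clustering within centres is expected.
- **Analysis.** Under Analytical statistics, the arms are first compared by Student's t-test for independent data with 95% confidence intervals. An explanatory model then complements that comparison and also answers the principal objective. Because subjects are clustered in centres, this model is fitted by GEE. The reason given for trusting the robust standard errors is that they are ones "which are stable even if the correlation chosen" in advance is incorrect, or if its strength differs between clusters.
- **Not stated.** No bias correction, reference distribution or degrees of freedom is named for the GEE tests.

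**The concern.** Robustness to a wrong working correlation is an asymptotic property in the number of clusters. The 400 subjects do not supply it; the 14 centres would have to. With few clusters two things go wrong, both towards false positives. The sandwich variance is built from residuals that the fitted model has already shrunk, so it is biased low. A normal critical value also ignores that the between-centre variance is estimated on about 12 degrees of freedom.

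The t-test for independent data ignores clustering, so GEE is the only effectiveness analysis in the article that allows for the clustering the sample size section expects. If its standard errors are too small, neither effectiveness analysis holds the 5% level used to size the trial, and the error runs towards declaring the training effective.

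**Working it through.** **Inputs.** 7 centres per arm (Design); 400 subjects (Studied subjects); SD 12, difference 5 points, alpha 0.05, power 80%, design effect about 2, loss 10% (Sample size and sampling). Alpha is taken as two-sided because that reproduces the stated sample size.

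**Step 1. The plan's own figure.** n per group = 2 × (1.960 + 0.842)² × 12² / 5² = 90.4, so 91, against the stated "It is therefore necessary to include ~90 subjects per group". Then 90 × 2 = 180, and 180 / 0.90 = 200. The sample size reproduces. The article states no error rate or coverage for the GEE analysis, so there is no GEE figure to reproduce.

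**Step 2. Bias of the uncorrected sandwich variance.** With J equal centres per arm and treatment as the only term, the robust variance of the arm difference is (J − 1)/J times the unbiased between-centre variance. For J = 7 this is 6/7 = 0.857.

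**Step 3. Type I error.** The correctly scaled statistic follows t on 2J − 2 = 12 df. The uncorrected Wald z-test therefore rejects when |t12| > 1.96 × √(6/7) = 1.815.
- Type I error = 2 × P(t12 > 1.815) = 9.47%.
- Coverage of the nominal 95% interval = 90.5%.
- Width relative to the correct interval = 1.815 / 2.179 = 0.833, so 16.7% too narrow.

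**Step 4. Both parts of the correction are needed.** Removing the 6/7 bias but keeping 1.96 gives 2 × P(t12 > 1.96) = 7.4%, with intervals 10% too narrow (1.96 / 2.179 = 0.90). Removing the bias and using t on 12 df gives exactly 5% in this balanced, unadjusted case.

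**Step 5. Sensitivity.** Except in the last row, these are simulations of exchangeable GEE with an uncorrected sandwich and a normal reference, 4,000 null trials per row (Monte Carlo standard error about 0.5 percentage points). The ICC is 0.036 unless stated, which is what a design effect of 2 implies at 28.6 per centre: 1 / (28.6 − 1). Centre-size variation, covariates and pair effects are assumptions, because the article gives no figures for them.

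| Scenario | Type I error |
|---|---|
| Equal centres | 9.6% |
| Equal centres, 5 individual covariates | 8.8% |
| Centre-size CV 0.3 | 10.0% |
| Centre-size CV 0.5 | 10.7% |
| CV 0.3, 5 individual covariates | 10.0% |
| The same plus 1 centre-level covariate | 12.2% |
| CV 0.3, ICC 0.01 or 0.10 | about 9.7% |
| CV 0.3, pairs explain 25% of between-centre variance, ignored | 8.3% |
| CV 0.3, pairs explain 50% of between-centre variance, ignored | 6.1% |
| The 7 pairs as the clusters (closed form, 6 df) | 12.0% |

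In the last row the interval is 1.815 / 2.447 = 0.74 of its correct width, or 26% too narrow. The result hardly depends on the ICC. It does depend on how the pairs and centre-level terms are handled.

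**Step 6. Candidate corrections in the balanced case.** The Kauermann-Carroll variance is unbiased here; with t12 it gives 5% and a width of 2.179 / 1.815 = 1.20 times the uncorrected one. The Mancl-DeRouen variance is larger by a further 7/6. With t12 the critical value is 2.179 × √(7/6) = 2.353, giving 3.6% and a width of 2.353 / 1.815 = 1.30. The two are not interchangeable.

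**The case against.** The strongest objection is that the faulty procedure is inferred. The article says robust; it does not say uncorrected or name a normal reference, and the corrected estimators are themselves robust variances. A separate analysis plan could name one, and an article need not carry that detail. It stands that the procedure is a plain reading rather than a stated one. But the article does more than leave a detail out: it offers a reason for trusting the standard errors that does not carry over to its own 14 clusters.

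Second, a reader might infer that the article claims stability with few clusters. It does not: stability is claimed against a wrong or varying correlation. The fault is in relying on that property with 14 centres.

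Third, a reader might take 9.5% as the trial's error rate. The documents do not support one figure. The design is pair-matched, the article does not say how pairs or centre-level terms enter the model, and the supportable statement is a range.

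Fourth, a reader might infer that GEE alone supplies the main p-value and interval. The article gives the first effectiveness comparison to the t-test and calls the model complementary, while also having it answer the principal objective. That the t-test ignores clustering is a separate defect, and it leaves GEE as the only clustered analysis.

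**Conclusion.** The point holds in conditional form. With 7 centres per arm, GEE read plainly (uncorrected sandwich variance, normal reference) does not hold the 5% level. With equal centres, no centre-level covariates and no pair effect, the type I error is about 9.5% and the 95% interval about 17% too narrow. Across the scenarios tried it ran from about 6% (effective matching that is ignored) to about 12% (a centre-level covariate, or pairs as the clusters), and it was above 5% in every one. If an unseen analysis plan already specifies a suitable correction and reference distribution, confirming that closes the point.

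**What to change.** Keep GEE for the effectiveness analysis and specify, before the analysis, the Kauermann-Carroll bias-corrected robust variance with a t reference on 12 df, less one for each centre-level covariate added. This gives 5% in the balanced, unadjusted case and is conservative if matching is effective and ignored. Mancl-DeRouen with the same reference may be chosen, knowing it is more conservative.

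Alternatively, use a centre-level analysis that respects the 7 randomised pairs: a paired t-test on adjusted centre means, with 7 − 1 = 6 df. The 12 df applies only to an analysis that ignores the pairs. State which analysis is primary.

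The cost is a sentence in the analysis section and a software setting, with no new data or centres. For the unpaired Kauermann-Carroll version, intervals are about 20% wider than the uncorrected ones, which is their correct width in the balanced case.
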